## 2. Methodology

The study will use an experimental research design to assess the effect of the school-based SRH services on occurrence of the adolescent pregnancy among the school girls aged 15–19 years. The Cluster Randomized Controlled Trial (CRCT) design with qualitative and quantitative components will be used as a gold standard in conducting this impact evaluation research so as to maximize comparability between the intervention and control groups, and hence give a strong evidence of a causal relationship between the intervention and the outcome [30,31,32].

The unit of randomization will be the 18 clusters (school) and 1080 individuals (girls); therefore, the cluster (school) of the eligible girls will be randomly allocated to either the intervention (9 schools) or the control (9 schools) arms of the study.

Blinding will be done to prevent systematic biases stemming from foreknowledge of group allocations among the participants and research aim outcomes as per RCT study standards [31]. Pre-determined information, such as the research hypothesis, will be concealed from the participants, data collectors, teachers and data analysts so as to prevent biases at all levels of the research. The participants will not be made aware of the research hypothesis and will be assigned any group accordingly.

In order to avoid misleading biases, the study will use the Intent To Treat (ITT) approach for analysis. Every participant allocated to a treatment group is considered to be part of the trial. ITT will be used in an attempt to avoid potential bias and identify the true effect of the intervention.

The research will use a pre-test-post-test control group approach [33]. This is where pre-intervention (baseline) measures on the prevalence of pregnancy will be conducted to allow for explicit evaluation of the pre-to-post changes.

Qualitative data will be collected through in-depth interviews of key informants in the community and discussions with groups of adolescent boys, parents, community members and school leadership. Standard guides with open-ended questions will be used for conducting the interviews and discussions. The participants of the interviews and discussions will be purposively selected based on their role in preventing adolescent pregnancy in the community.

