**Random Sampling:** The allocation of schools (clusters) to either the intervention and control groups will be randomly conducted. After selection of the 18 schools, nine schools will be randomly allocated to the intervention group and the other nine will be allocated to the control group. The names of the 18 selected schools will be placed in a basket and randomly selected and allocated to either group of study.

Blinding will be conducted at the random allocation of the school clusters to either the intervention group or control group. The research assistants, Biostatistician and school administration will be blinded to the study hypotheses.

**Systematic Sampling:** Systematic sampling will be used to select the 1,080 adolescent girls from the 18 schools (clusters). This is a probability sampling method in which sample members from a larger population are selected according to a random starting point and a fixed periodic interval [33]. Upon selection of the 18 schools that are considered to be clusters, 60 eligible girls will be systematically selected from each school using class lists.

A list of all girls aged 15–19 years in form two, three and five will be generated by the school administration. This periodic interval will be determined beforehand as 2, which means that assuming the starting point is 1 as the first serial number on the class lists, every girl with an even serial number will be selected to participate in the study, that is, 2, 4, 6, 8, etc. The girls will have an equal chance to be selected to participate in the study. A total of 1080 secondary school girls will be systematically selected from the 18 schools in equal numbers of 60 girls aged 15 to 19 years per school. Figure 1 illustrates the sampling framework to be used during the study.

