### 2.7. Recruitment of Study Participants

The study will be conducted in the 18 selected secondary schools as clusters; each school will be randomly assigned to the intervention study group or the control study group. Each school cluster will be independent, with no crossover of staff/students and defined as a natural cluster for the purpose of the trial. Each arm of the study will have nine schools (clusters).

The selection of the 18 study schools (clusters) will be conducted as per the criteria described in Section 2.6 (sampling) and each of the 18 schools will be randomly assigned to either the intervention (with SBSRH package) or the control group (without SBSRH package). This means that both the intervention arm and control arm had will have a total of nine schools each.

Within each school, the 1080 study participants will be selected systematically based on the inclusion criteria described in Section 2.2 (selection criteria). The recruitment of the study participants will be done independently by the researchers and research assistants. This will be done at school using the systematic sampling framework described in Section 2.6. The process is anticipated to take place within one month for all the 18 schools. Only girls who meet the inclusion criteria will be enrolled into the study. The participants will be informed about the study objectives without revealing the study hypotheses. Upon recruitment, each participant with their parent will be required to ascent and consent, respectively, by signing formal ascent and consent forms. Data collection (base line) will be done, an SBSRH package will be provided in the nine intervention clusters (schools) and follow-up is done for 12 months. An end of study assessment will be conducted after twelve months and data will be analyzed.

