#### 2.8.1. Tier 1: In-School ASRH Education Session

The health education sessions will provide information and create awareness on HIV, pregnancy, safer sex, Gender Based Violence, HIV, pregnancy, sexually transmitted infections (STIs), gender norms, effective communication and safe sex practices, sexuality and self-assertion. The Stepping Stones curriculum and the National sexuality framework in Uganda will be used as the standardized behavioral change package using the interpersonal peer to peer approach. 10 sessions (communication, how we act, sex, love, gender based violence, contraceptives, HIV prevention, safer sex practices, assertiveness, supporting one another and self-reflection) will be conducted for the participants by fellow trained peers and knowledge change as well as behavioral change assessed. Implementation of sessions will be done in small groups of 15–20 girls (peers). Peer facilitators will be trained and supported to conduct the small group discussions on SRH and HIV prevention. The researcher, research assistants, SRH nurse and senior woman teacher in-charge of SRH will supervise these sessions.

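### Blinding is said to prevent bias from knowing the allocation, at all levels, but the only concealed item named is the hypothesis, and staff listed as blinded supervise the intervention sessions

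*Protocol article*

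**What the plan says.** All references are to the protocol article.

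- **Purpose (section 2, Methodology).** "Blinding will be done to prevent systematic biases stemming from foreknowledge of group allocations among the participants and research aim outcomes".
- **Means (section 2).** "Pre-determined information, such as the research hypothesis, will be concealed from the participants, data collectors, teachers and data analysts", with the aim given as "so as to prevent biases at all levels of the research".
- **Allocation (section 2.6, Random Sampling).** "Blinding will be conducted at the random allocation of the school clusters to either the intervention group or control group". No mechanism follows, and nobody is named as unaware of a school's arm. The next sentence names the staff concerned and what is kept from them: "The research assistants, Biostatistician and school administration will be blinded to the study hypotheses".
- **Recruitment (section 2.7).** "The recruitment of the study participants will be done independently by the researchers and research assistants". Participants are told the objectives but not the hypotheses.
- **Delivery (section 2.8.1).** "The researcher, research assistants, SRH nurse and senior woman teacher in-charge of SRH will supervise these sessions".
- **Contrast between arms (sections 2.8.1 to 2.8.3).** Intervention schools get ten small-group sessions and a weekly clinic on the premises. Control schools get nothing from the research team.
- **Measurement (section 2.8.3, Data Collection Tools).** The quantitative tool is a self-administered questionnaire, completed at 0, 6 and 12 months. Service use is also recorded on clinic days and in a utilization register.

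**The concern.** The stated purpose is protection against knowledge of the arm. The stated means is silence about the hypothesis. These are different things: a person can be told nothing of the hypothesis and still know exactly which arm a school is in. The people who run the intervention sessions necessarily know it.

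An open design is unavoidable for an intervention of this kind and is not the fault. The fault is that the article claims a property the design does not have. Incidence of pregnancy and sexual behaviour change are two of the three primary outcomes in section 2.1.2, and both are sensitive self-reports. Girls who have had a year of sessions on contraception and safer sex may report differently from girls who have had none. If they under-report, a false benefit can appear; if they disclose more freely, a real benefit can be hidden. A reader who accepts the blinding statement will not look for either.

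**Working it through.** **1. Stated protection against stated procedure**

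| Role | Listed as blinded | To what | Task elsewhere | Can the role be unaware of the arm? |
|---|---|---|---|---|
| Research assistants | 2.6 | Hypotheses | Recruit (2.7); supervise intervention sessions (2.8.1) | Not where they supervise |
| Teachers | 2 | Information such as the hypothesis | Senior woman teacher supervises sessions (2.8.1) | Not the senior woman teacher in an intervention school |
| School administration | 2.6 | Hypotheses | Draws up the list of girls (2.6); head teacher's willingness is a selection condition (2.6) | Not once the clinic is running on the premises |
| Participants | 2 | Information such as the hypothesis | Attend sessions and may use the clinic | Not in intervention schools; not documented for control schools |
| Biostatistician, data analysts | 2.6 and 2 | Hypotheses; information such as the hypothesis | Analysis | Possibly, but masking of the arm is not stated |

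For none of these roles is the arm itself named as concealed. For research assistants and the senior woman teacher, the delivery role rules concealment out.

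**2. Order of allocation and enrolment**

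Sections 2.6 and 2.7 describe the draw of schools before the selection of girls. Section 2.7 then puts recruitment, consent and baseline before the package is provided. Neither section says when the result of the draw is disclosed. Whether recruiters know the arm at enrolment therefore cannot be settled from the text.

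**3. Illustration of the stake**

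The article gives no figure for reporting bias, so there is none to reproduce.

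Inputs from the article:
- 9 schools × 60 girls = 540 per arm
- ICC 0.01 and cluster size 60, so the design effect is 1 + 59 × 0.01 = 1.59
- 29% as the regional prevalence (section 2.4.2)

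Assumptions not in the article:
- no true effect
- relative under-reporting r of 10% or 20%, in the intervention arm only
- risks of 5% and 10% as alternatives to 29%, because the listed outcome is incidence while 29% is a prevalence

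Effective size per arm: 540 / 1.59 = 339.6.

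With p the true risk and q = p(1 − r):
- SE = √{[p(1 − p) + q(1 − q)] / 339.6}
- z = (p − q) / SE
- rejection probability = Φ(z − 1.96) + Φ(−z − 1.96)

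Worked case, p = 0.29 and r = 0.10:
- q = 0.261
- SE = √[(0.2059 + 0.1929) / 339.6] = 0.0343
- z = 0.029 / 0.0343 = 0.846
- rejection = Φ(−1.114) + Φ(−2.806) = 0.1327 + 0.0025 = 0.135

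| Assumed risk | r | False difference | z | Rejection (nominal 5%) |
|---|---|---|---|---|
| 29% | 10% | 2.9 points | 0.846 | 13.5% |
| 29% | 20% | 5.8 points | 1.725 | 40.7% |
| 10% | 10% | 1.0 point | 0.445 | 7.3% |
| 10% | 20% | 2.0 points | 0.911 | 14.9% |
| 5% | 10% | 0.5 point | 0.306 | 6.1% |
| 5% | 20% | 1.0 point | 0.629 | 9.6% |

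With a t reference on 18 − 2 = 16 degrees of freedom, the two 29% rows become about 12.5% and 36.8%. The 5.8-point false difference is 58% of the 10-point effect the trial is sized for (5.8 / 10).

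**The case against.** Much can be said for the plan, and some of it stands.

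- **A reader might infer that only the hypothesis is concealed.** The text does not go that far. Section 2 offers the hypothesis as an example, and section 2.6 separately asserts blinding at the random allocation. What stands is narrower: no other concealed item is named, and no mechanism is given. A full protocol might supply one, but it could not make session supervisors unaware of the arm.
- **A reader might infer that teachers recruit.** They are not said to. Of the teachers, only the senior woman teacher is named as supervising sessions. Nothing gives the school administration a part in delivering sessions.
- **A reader might infer that every girl knows her arm.** This is evident in intervention schools only. No passage says control girls are told that a comparison arm exists, and withholding the hypotheses may dampen demand effects.
- **A reader might infer that all outcomes are self-reported.** Service use also has clinic-day and register data, so the reporting argument is confined to pregnancy and sexual behaviour.
- **A reader might infer that session supervisors also collect the follow-up data.** The article does not say so, and self-administration limits interviewer influence. It does not rule the overlap out either.
- **Recruitment is weak support.** Girls are taken from class lists at a fixed interval, which limits discretion, and baseline precedes delivery.
- **The arithmetic is illustrative.** The under-reporting rates have no basis in the documents, and the excess over 5% is small when the risk is low.

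None of this reconciles the stated purpose with the stated means.

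**Conclusion.** The concern holds in a limited form: the article claims protection that its own procedures do not provide. The firm internal conflict is between the list of blinded people in sections 2 and 2.6 and the supervisory roles in section 2.8.1. It concerns research assistants and the senior woman teacher. The all-levels claim is wrong as written.

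Differential reporting of pregnancy and sexual behaviour is possible; the documents neither show that it will occur nor fix its size. The range of about 6% to 41% false positives against a nominal 5% depends on assumed under-reporting of 10% to 20%, confined to the intervention arm, and on an assumed risk between 5% and 29%. It shows that the matter can be material, not that it is.

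The sample size is not affected. This should be corrected; it is a matter of accurate claims and inexpensive safeguards, and does not invalidate the open design.

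**What to change.** 1. State that participants, schools and delivery staff are not blinded to allocation, and remove the claim that bias is prevented at all levels.
2. Limit the blinding claim to the analyst, who works with arms coded A and B until the primary analysis is locked.
3. Specify that listing of girls, consent and the baseline survey are completed in all 18 schools before the allocation is disclosed.
4. Assign the existing research assistants so that none handles the 6- and 12-month questionnaires in a school where they supervised sessions.

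The cost is protocol wording, a coded data set and a staff rota. No new staff, instrument or participants are needed. The downside is some scheduling effort.

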## Abstract

Uganda has persistently had high adolescent pregnancy prevalence; 25% for the last 10 years. This protocol presents the design of a Cluster Randomized Controlled Trial (CRCT) to investigate the effectiveness of School-Based Sexual and Reproductive Health (SBSRH) interventions on prevention of pregnancy among school girls aged 15–19 years in the Hoima District, Uganda. 18 secondary schools (clusters) will be selected using cluster sampling and allocated 1:1 into control or intervention group stratified by geographical location. 1080 (60 each cluster) participants/girls aged 15–19 years will be selected using simple random sampling. The intervention group will receive tailored SRH information, in-school medical care and referral over 12 months. The control group will receive no intervention from the research team; however, they can access alternative services elsewhere if they wish. Data will be obtained at baseline, 6 months and 12 months. The outcomes are reduction in occurrence of pregnancy, utilization of SRH services and sexual behavioral change. To our knowledge, this is the first CRCT providing combined SRH interventions for prevention of adolescent pregnancy in Uganda. If effective, it could have great potential in preventing adolescent pregnancy. Trial Registration: Pan African Clinical Trial Registry (PACTR201810882140200) Registered on 16 October 2018.

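### The rule for selecting girls contradicts itself, and one fixed interval of 2 cannot give 60 girls per school in schools of different size

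*Protocol article*

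**What the plan says.** The protocol article describes the selection of girls within schools in three places.

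- **Abstract:** "1080 (60 each cluster) participants/girls aged 15–19 years will be selected using simple random sampling".
- **Section 2.6 (Sampling Techniques), paragraph on systematic sampling:** the method is one in which members are "selected according to a random starting point and a fixed periodic interval". The school administration produces a list of girls aged 15–19 in forms two, three and five. The text continues: "This periodic interval will be determined beforehand as 2"; "assuming the starting point is 1 as the first serial number on the class lists"; and "every girl with an even serial number will be selected to participate in the study, that is, 2, 4, 6, 8, etc". It adds: "The girls will have an equal chance to be selected to participate in the study". The same paragraph requires 60 girls from each of the 18 schools, 1080 in all.
- **Section 2.7 (Recruitment):** recruiters are referred back to the systematic framework of Section 2.6, so that section is the operative rule.

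Section 2.4.2 uses a fixed cluster size of 60 in the design effect, and Section 2.5 arrives at 18 clusters and 1080 girls.

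**The concern.** Simple random sampling and systematic sampling are different procedures, and the article names both for the same step. Within Section 2.6, a method defined by a random start is followed by a start that is assumed, not drawn, and by a list of serial numbers that this start does not produce. Two research assistants following the text could select different girls.

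The rule also combines a fixed interval with a fixed quota. Both can hold only if every school's list has nearly the same length, and nothing in the article says so.

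Three things are at stake: whether the claim of equal chance is true, whether the cluster size used in the sample size calculation can be reached, and whether selection is open to influence. The school administration makes the list, and under the even-number rule anyone who knows the rule can tell from a girl's position whether she will be chosen.

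**Working it through.** **The plan's own figure.** Inputs from Section 2.4.2: proportions 0.29 and 0.19, z values 1.96 and 0.842, ICC 0.01, cluster size 60.

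- Per arm, individually randomised: (1.96 + 0.842)² × (0.29 × 0.71 + 0.19 × 0.81) / 0.1² = 282.5.
- Design effect: 1 + 59 × 0.01 = 1.59, and 282.5 × 1.59 = 449 per arm, or 898 in total.
- With 10% added: 898 × 1.10 = 987.8, taken as 988.
- Clusters: 988 / 60 = 16.5, rounded to 17 and then to 18 for equal arms. 18 × 60 = 1080.

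The figure of 1080 reproduces and is not in dispute. It does rest on 60 girls per school.

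**Start and serials.** A start of 1 with interval 2 gives 1, 3, 5, 7 and so on. The article gives 2, 4, 6, 8, which is the sequence for a start of 2.

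**Chance of selection.**

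- Even-number rule taken literally: probability 1 for even serials and 0 for odd serials. On a list of 120, 60 girls could not be chosen.
- Start drawn at random from 1 and 2, interval 2: probability 1/2 for every girl.

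**Yield against the quota.** For a list of L names, the even-number rule selects floor(L/2). With a drawn start the yield is floor(L/2) or, for odd L with start 1, one more. The article gives no list lengths, so the values of L below are assumptions.

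| Assumed L | Girls selected, even rule | Interval needed for 60 (L/60) |
|---|---|---|
| 80 | 40 | 1.33 |
| 100 | 50 | 1.67 |
| 120 | 60 | 2 |
| 150 | 75 | 2.5 |
| 200 | 100 | 3.33 |
| 240 | 120 | 4 |

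Exactly 60 results from the even rule only for L = 120 or 121. These are girls selected, not enrolled: Sections 2.2 and 2.3 also require English literacy and signed consent or assent, so a list of 120 would yield fewer than 60 participants if any selected girl failed these.

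**Longer lists.** If selection stopped at the 60th girl, the even rule would end at serial 120. On an assumed list of 200, the 80 names after that could not be reached (80/200 = 40%). The article states no such stop, so this shows only what one way of meeting the quota would do.

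**Effect on the total.** 1080 exceeds 988 by 92. If four schools gave 40 girls in place of 60, the total would be 1080 − 4 × 20 = 1000, still above 988. Smaller clusters also lower the design effect.

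**The case against.** The strongest reply is that the even-number sentence is a muddled worked example. Section 2.6 defines the method by a random start, and the sentence is conditional on an assumed start. With a drawn start, every girl has probability 1/2 and the equal-chance statement is true. This stands as a possible reading. Against it, the sentence says the even-numbered girls will be selected, and it does not work as an example because a start of 1 gives odd serials. The interval problem remains on either reading.

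Second, list lengths are unknown and no cut-off is stated. A reader might infer that a large share of girls is excluded, for example that 70% of a list of 200 could never be chosen (140 of 200, from the literal even rule combined with a stop at serial 120), or that form five would be lost. The article does not support this as a finding: it needs an assumed list length, an unstated stop and an assumed list order. Section 2.6 speaks of class lists, so serials may run within each class.

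Third, a reader might infer that the rule biases the trial result. Schools are the randomised unit and the same rule applies in both arms, so the rule does not by itself bias the comparison. Section 2.6 blinds the school administration to the hypotheses, and Section 2.7 has researchers and research assistants recruit independently. Nothing suggests that schools would order lists strategically. What stands is that a predictable rule applied to a list made by the school is an avoidable opening for selection.

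Fourth, Figure 1 is not shown, and reserve lists or the handling of refusals are details that an article may leave to the full protocol. Their absence is not part of this point. The interval, start, serials and quota are all stated, and they conflict.

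**Conclusion.** The point holds as a contradiction in the stated sampling method together with a rule that cannot do what it promises.

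- **Certain from the text:** the Abstract and Sections 2.6 and 2.7 name different methods; the even serials do not follow from a start of 1; and one interval of 2 cannot give 60 girls in schools whose lists differ appreciably in length. It fits lists of about 120, before eligibility and consent losses.
- **Conditional:** that odd-numbered girls have no chance, and so that the equal-chance statement is false, holds only if the even-number rule is applied literally. It falls away if the start is drawn at random.
- **Not shown:** bias in the comparison of arms, or a loss of power. The margin of 92 girls over the required 988 absorbs a shortfall in a few schools. Whether it is enough depends on list lengths that the article does not give.

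The consequence is moderate: an ambiguous and predictable selection rule and uncertain cluster sizes, in a step that is easy to state correctly.

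**What to change.** Name one method and use it in the Abstract and in Sections 2.6 and 2.7. Delete the even-number rule and the interval of 2. Either of these would do:

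1. The study team draws a simple random sample of 60 from each school's full list of eligible girls.
2. Systematic sampling is kept, with interval N/60 for a school with N eligible girls and a start drawn at random by the study team. Where N/60 is not a whole number, draw the start between 0 and N/60, add N/60 repeatedly and round each value up. For N of at least 60 this gives exactly 60 serials, each girl having probability 60/N.

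Option 2 needs less rewriting, because only the Abstract's method and the start and interval in Section 2.6 change. Under either option the equal-chance statement becomes true within each school, and position on the list no longer tells the school who will be chosen. The cost is one random draw per school, 18 in all, and a few lines of protocol wording.
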